**Fig. 1 Fig1:**
[figure not shown]
The IRRA*flow* system consists of a dual lumen catheter for irrigation and aspiration respectively (courtesy of IRRAS)

The study is an investigator-initiated, prospective multi-center, 1:1 randomized, comparative phase 2 trial evaluating the efficacy and safety of active irrigation external ventricular drainage (intervention—IRRAflow) compared to passive external ventricular drainage (control—EVD) (Fig. 2). The investigators are unblinded for the treatment, but there is blinding concerning evaluations of endpoints where possible.

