#### Follow-up assessments

After placement of the VC, the patients in the two arms will receive the same treatment and monitoring. They will be admitted to the intensive care unit and later transfer to the stationary neurosurgical department before discharge to a rehabilitation facility. Patients will be followed closely regarding the primary, secondary, and exploratory endpoints. During the admission period, the patients will be followed with a CT scan at day 0, day 2, day 4, day 6, and day 8 to evaluate the size of the hematoma using CT volumetrics.

A scheduled follow-up will be applied for all included patients including a clinical status at the time of inclusion, discharge, and 3 months post-procedure. The follow-up will include GCS and mRS at inclusion, discharge, and 3 months. Furthermore, eGOS will be evaluated at discharge and 3 months. The rate of shunt dependency, adverse events, and serious adverse events will be evaluated continuously during the inclusion period. Mortality rates will be evaluated at 30 days and 3 months.

All patients will receive best practice care following trial exclusion or termination. Post-trial care will be independent of trial participation and similar to the care offered to patients who were not enrolled or withdrew consent. Patients who are harmed during the trial will not be offered compensation, which is specific for the trial. However, patients might be eligible for compensation under similar rules and conditions as patients who are not enrolled in the trial as defined by Danish law (Patienterstatningen).

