#### Sample size and statistical considerations

The sample size of the study was determined based on the primary outcome. We considered a two-sided log-rank test for comparison of the time-to-catheter occlusion between the two treatment groups. Furthermore, we assumed an equal length of follow-up together with an occlusion risk of 10% and 35% in the intervention and control groups. Patient mortality was assumed to be independent of the considered time to catheter occlusion and to correspond to a 30% dropout. We used a significance level of 20% due to the exploratory nature of the study. Then, for a power of 80%, Schoenfeld’s approach resulted in a required sample size of 58 (i.e., 29 subjects with drain per treatment group).

Data will be analyzed according to the intention-to-treat principle. For the primary outcome (time to catheter occlusion), time-to-event analysis will be used, in which drains are considered the basic experimental units. Times corresponding to drains without occlusion during follow-up will be considered censored. Especially, since catheter occlusion is independent of patient mortality, patient death is treated as a censoring event. Time to occlusion will be described by Kaplan-Meier plots and investigated by Cox regression. Estimated beneficial treatment effects with a two-sided *p*-value ≤ 20% will be considered an interesting finding worth further investigation.

Further outcome measures (secondary/exploratory) will be used for descriptive and exploratory purposes only; no formal statistical hypotheses will be tested.

Secondary endpoints (subject-based unless otherwise specified) will be handled as follows:

Kaplan-Meier estimates and Cox regression will be used to describe the time to recurrence of hemorrhage and time to death (with a follow-up time of 3 months).

Occurrence of catheter-related infections and shunt dependency will be reported as proportions, and length of stay in ICU will be reported as means. Clearance of ventricular blood will be described with the help of linear mixed effect models. Measures of functional status will be dichotomized and analyzed by baseline-adjusted logistic regression. All estimates will be reported together with corresponding confidence intervals (CIs).

Exploratory endpoints (mainly drain-based) will be handled as follows:

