Proportions and CIs will be reported for technical success, procedure success, and necessity of revision procedures. Procedure time, duration of VC in place, and number of required flushes will be described by means and CIs.

Reported CIs will include a Bonferroni adjustment to maintain the family-wise coverage probability at 95%.

We expect based on our prior experiences that the proportion of missing values in this study will be very low and that missing values occur completely random. All statistical analyses will be run as complete case analyses.

For early safety monitoring, an interim analysis is done when 20 subjects have been enrolled in the study (10 subjects per arm). The analyses will be performed in an intent-to-treat fashion.

Monitored safety outcomes are mortality as well as the total number of adverse and serious adverse events related to catheter treatment (infections, bleedings in relation to intervention, displacements of catheters, catheter misplacement). For *p*-values below 20%, an early stop of the study will be considered (non-binding); otherwise, the study continues until the study end.

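### Apart from deaths, the 20-patient safety comparison counts only catheter-related events; all-cause haemorrhage, infection and serious adverse events by arm should stand beside them.

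*Protocol article*

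**What the plan says.** Under Sample size and statistical considerations, the protocol article states that "an interim analysis is done when 20 subjects have been enrolled in the study (10 subjects per arm"). It then defines the outcomes as mortality and the total number of "adverse and serious adverse events related to catheter treatment (infections, bleedings in relation to intervention, displacements of catheters, catheter misplacement"). The rule is: "For *p*-values below 20%, an early stop of the study will be considered (non-binding"). Neither the test nor its sidedness is named, and nobody is named as judging relatedness.

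Four other places bear on this:

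- **Blinding** (Methods and study design, text after Fig. 1): "The investigators are unblinded for the treatment, but there is blinding concerning evaluations of endpoints where possible".
- **Repeat haemorrhage.** The Exploratory endpoints list a rate of repeated haemorrhagic events, and the statistical section analyses "time to recurrence of hemorrhage and time to death (with a follow-up time of 3 months"). Neither carries a relatedness condition, and neither is listed for the interim look.
- **Imaging** (Follow-up assessments): patients in both arms are "followed with a CT scan at day 0, day 2, day 4, day 6, and day 8".
- **Data monitoring committee.** The committee's look after 10 patients uses severe adverse events in each group, with the same 20% threshold and no stated relatedness filter.

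**The concern.** Intraventricular haemorrhage is an inclusion criterion, so every patient already has intracranial blood. A new or larger bleed may come from the underlying disease, the puncture or the irrigation, and choosing between these is a matter of opinion. If the event must be called related before it counts, that opinion decides whether it enters the safety comparison.

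A randomised control arm removes the need for this step. Bleeding from the disease is expected equally in both arms, so a difference in all-cause counts estimates the device effect without an attribution. The filter can lose real device events in two ways. Knowledge of the arm may influence the call. Even with fully blinded calls, discarding a share of true events from both arms leaves fewer events and less chance of seeing a difference.

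The exposure is confined to non-fatal events. It matters because the trial already records repeat haemorrhage without the filter and images both arms on the same days, yet this information is not part of the 20-patient comparison.

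**Working it through.** **The plan's own figures.** The article gives no power or error rate for the interim look, so there is nothing to reproduce there. Its total of 58 does reproduce: the hazard ratio is ln(0.90)/ln(0.65) = 0.245, Schoenfeld's formula at two-sided 20% and 80% power gives 9.09 events, 9.09/0.225 = 40.4, and 40.4/0.70 = 57.7. That figure concerns occlusion and does not bear on safety.

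**Inputs.** From the article: 10 patients per arm and a trigger at p < 0.20. Assumed: a two-sided Fisher test on patients with at least one bleed, the bleed risks, the share attributed away and the background rate. The plan's statistic is a total count over several event types, so what follows shows direction and rough size, not the plan's operating characteristics.

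**Step 1: effect of one reclassified event at the boundary (device v control).**

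| Test | Before | After one device event is removed |
|---|---|---|
| Fisher | 4 v 0, p = 0.087 | 3 v 0, p = 0.211 |
| Fisher, one control event | 5 v 1, p = 0.141 | 4 v 1, p = 0.303 |
| Chi-square, uncorrected | 2 v 0, p = 0.136 | 1 v 0, p = 0.305 |
| Conditional binomial | 4 v 0, p = 0.125 | 3 v 0, p = 0.250 |

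Away from the boundary one call changes nothing: Fisher 5 v 0 becomes 4 v 0, still p = 0.087.

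**Step 2: chance of a harm trigger.** Sum Bin(a; 10, pD) × Bin(b; 10, pC) over all tables with a > b and Fisher p < 0.20, where pD and pC are the device and control risks. With 40% v 10% and all bleeds counted, the result is 39%.

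If a share s is attributed away, pD becomes 0.40(1 − s). Where the filter acts on both arms, pC becomes 0.10(1 − s).

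| Share attributed away | Device arm only | Both arms |
|---|---|---|
| 1 in 10 | 31% | 32% |
| 1 in 4 | 19% | 22% |
| 1 in 2 | 6% | 8% |

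**Step 3: cost of counting everything.** An independent background rate g turns each risk p into 1 − (1 − p)(1 − g).

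| g | Risks | Harm trigger |
|---|---|---|
| 10% | 46% v 19% | 35% |
| 20% | 52% v 28% | 31% |
| 40% | 64% v 46% | 22% |

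**Step 4: other assumed risks.**

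| Risks | All counted | 1 in 4 filtered, both arms | All counted, background 10% and 20% |
|---|---|---|---|
| 30% v 10% | 19% | 10% | 19% and 18% |
| 50% v 10% | 61% | 39% | 53% and 45% |
| 50% v 20% | 41% | 26% | 36% and 31% |

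In each of these, losing a quarter of events costs more than a background of 10–20%.

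**The case against.** Several counter-arguments are sound.

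- **Mortality is unfiltered at the same look.** A fatal bleed counts there whatever its cause. A reader might infer that the whole comparison rests on attribution; the text does not support that.
- **No assessor is named.** A reader might infer that unblinded staff make the relatedness call. The article does not say so. It promises blinded endpoint evaluation where possible, and an article may leave adjudication to the full protocol. The wording about bleedings and the intervention could also be temporal rather than causal. This stands, but the both-arms column shows that blinding alone would not recover the lost power.
- **A single call cannot be said to cancel a harm signal in general.** It does so only at the boundary, and at 10 per arm any single event has that leverage, filtered or not. The trigger is also non-binding, and the committee monitors adverse events more widely, so missing p < 0.20 does not silence it.
- **The illustration models bleeds alone.** In the plan's total count, displacements and misplacements are catheter events by nature and would survive a disputed bleed.
- **The trade-off depends on the assumptions.** A 20% background (31%) costs about as much as misattributing 1 in 10 (31–32%), and a 40% background (22%) about as much as filtering a quarter in both arms. An accurate filter would beat counting everything.
- **Catheter-related events are a legitimate outcome** when two catheter systems are compared.

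Together these argue for keeping the related count and adding to it. They do not explain why all-cause events are absent from the 20-patient comparison, or why the two looks use different event sets.

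**Conclusion.** The point holds for non-fatal events. The article itself fixes the interim outcomes, so this is not a detail left to another document. It restricts those outcomes to related events in a trial with unblinded investigators and no stated blinded assessor, and it leaves out a haemorrhage endpoint that the trial already collects. The 10-patient look has no such stated restriction.

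On the assumed Fisher test and 40% v 10% risks, attributing away a quarter of bleeds roughly halves the chance of a harm trigger, from 39% to 19–22%. Counting everything with a 10–20% background lowers it only to 35–31%. The ordering holds for the other risk pairs tried, but not for a high background or for very accurate attribution. None of these risks or shares comes from the article.

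This is a cheap improvement to a safety rule. It does not show that safety is unmonitored or that attribution has been or will be biased.

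**What to change.** In the interim paragraph of Sample size and statistical considerations, add three comparisons by arm, whatever the attributed cause: all new or repeat intracranial haemorrhages after catheter placement, all ventricular infections, and all serious adverse events. Keep mortality as it is and show the catheter-related count beside the all-cause counts. State whether bleeding in relation to the intervention is meant causally or temporally.

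Then reconcile this paragraph with Data monitoring committee, so that the 10-patient and 20-patient looks use the same event set or the reason for the difference is given.

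The change takes a sentence or two and draws on events that the article already says are recorded. The costs are some noise from background events, as in Step 3, and a slightly higher chance of a false trigger from the extra comparisons. The latter is tolerable because the trigger is non-binding and the committee can weigh all the counts together.

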## Background

Primary intraventricular hemorrhage (IVH) or IVH secondary to intracerebral hemorrhage (ICH) and subarachnoid hemorrhage (SAH) with extension to the ventricles are known to have a very poor prognosis, with expected mortality between 50 and 80% [1]. Yet, therapy directed at ameliorating intraventricular clot has been limited. IVH often results in increased intracranial pressure (ICP) by direct mass effect, by obstruction, and further by creating edema around the hematoma. These conditions can be complicated by hydrocephalus caused by CSF malabsorption [2] or obstruction of CSF pathways. Further secondary brain injury is related to the clotting cascade after endothelial damage and hemoglobin breakdown [3]*.* Thrombin causes inflammatory cells to infiltrate the brain, proliferation of mesenchymal cells, formation of brain edema, and scar tissue [3]*.* Thrombin binds to protease-activated receptors *(1)* and activates the central nervous system microglia and complement cascade. As a result, multiple immune pathways are activated, which contributes to apoptosis and necrosis. Heme influx in neurons after endothelial damage leads to iron release and neuronal insult [3].

CSF drainage is a key factor in maintaining acceptable ICP levels to prevent secondary brain damage. There are multiple approaches to facilitating CSF drainage and monitoring ICP. A ventricular catheter (VC) inserted into the lateral ventricle allows for drainage of CSF, but complication rates are high. VC occlusions in patients with IVH have been reported in 41% [4], of these 19% are having at least one VC replacement [4]. VC-related infection rates are found to be 10% for bacterial ventriculitis [5, 6].

The aim of this study is to evaluate the safety and feasibility in the use of active fluid exchange in the treatment of intraventricular hemorrhage.

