### The IRRAflow device

The IRRAflow system performs active, controlled fluid exchange, based on the notion that it is faster to wash out IVH, compared to gravity drainage alone. IRRAflow combines periodic, controlled irrigation and aspiration of the catheter probe with neutral physiological fluids. The continuous perfusion cleans the entire inner catheter probe’s surface while the fluid movement helps to disrupt potential clot or bacteria colony formation on the catheter probe’s intracranial external surface, thereby minimizing the problems associated with passive drainage: blockage and infection. IRRAflow perfusion is combined with continuous ICP monitoring that includes safety alarms.

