#### Data monitoring committee

An Independent Data Monitoring Committee (DMC) has been created with the main purpose of patient safety. The DMC will achieve this by monitoring especially adverse events and severe adverse events and further analyzing the benefit vs risk ratio of the treatment. The DMC will evaluate the safety of the study after the enrollment of 10 patients. The safety evaluation will be based on severe adverse events in each group. For *p*-values below 20%, early stop of the study will be considered (non-binding). Additionally, the DMC will provide an independent scientific review of the interim analysis and recommend continuation or discontinuation of the trial. If the trial passes interim analysis, the DMC will review the final data as well. The DMC will serve in an advisory capacity to the sponsor.

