Previous studies have investigated the use of fibrinolytics to help the removal of the blood in the ventricles. Data from the CLEAR II trial showed that low-dose rt-PA for the treatment of ICH with IVH had an acceptable safety profile compared with placebo and prior historical controls [9]. In the CLEAR III trial, removal of IVH was investigated using either alteplase or saline irrigation [2]. In this study, irrigation of the ventricles with alteplase via a routine EVD did not improve functional outcomes in patients with IVH. One-hundred-eighty-day case fatality was significantly lower in the alteplase group; however, most of these survivors ended up with severe disability (mRS 4 or 5 or eGOS lower and upper significant disability) [10]. The authors also found an association between the amount of clot removal and improved odds of mRS ≤3. The authors concluded that precise clinical definitions for the at-risk population need to be tested in a surgically standardized trial setting and further that a greater benefit could potentially be achieved with greater clot removal (e.g., increased number of patients with >80% removal). They also concluded that future investigation needed to improve the surgical placement of catheters to achieve effective clot reduction more frequently and more rapidly [10]. The IRRAflow system presents a novel approach to minimally invasive clot removal, which is inherently different from alteplase administration through standard EVDs. The continuous irrigation system allows for significant acceleration of IVH clearance as well as other toxins and cellular debris that may accumulate secondary to hemorrhagic stroke. For this phase 2 clinical trial, our main goals will be to evaluate the safety, efficacy, and feasibility of using the IRRAflow active fluid exchange system.

Different new innovations in IVH including novel procedural techniques, the use of the Integra Surgiscope, the use of the Artemis evacuator, the use of BrainPath, novel catheter technology, large bore external ventricular drains, and the CerebroFlo are techniques being tested to lower the morbidity and mortality in IVH patients [11].

Possible risks following the use of active irrigation could be hydrocephalus and increased ICP due to the constant supply of saline. To reduce the risk, saline infusion will be decreased when ICP is found to be 20 mmHg or above or stopped if ICP is still increasing regardless of the decrease in irrigation.

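### The event list for the 20-subject safety look omits raised ICP and hydrocephalus, the two risks the protocol itself attributes to irrigation

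*Protocol article*

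**What the plan says.** All references are to the protocol article.

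- **Risk statement (Discussion).** "Possible risks following the use of active irrigation could be hydrocephalus and increased ICP due to the constant supply of saline". The mitigation is that "saline infusion will be decreased when ICP is found to be 20 mmHg or above", and that the infusion is stopped if ICP keeps rising. No other risk of irrigation is named there.
- **Look at 20 subjects, 10 per arm (Sample size and statistical considerations).** The monitored outcomes are mortality and the total number of adverse and serious adverse events "related to catheter treatment (infections, bleedings in relation to intervention, displacements of catheters, catheter misplacement"). A p-value below 20% prompts a non-binding consideration of stopping.
- **Look at 10 patients (Data monitoring committee).** It rests on severe adverse events in each group, with no list of event types, and has the same non-binding 20% guide. The committee's general remit is "monitoring especially adverse events and severe adverse events" and weighing benefit against risk. It also reviews the interim analysis and the final data.
- **Bedside protection (The IRRAflow device).** "IRRAflow perfusion is combined with continuous ICP monitoring that includes safety alarms".
- **Monitoring in both arms (Follow-up assessments).** After catheter placement, "the patients in the two arms will receive the same treatment and monitoring". Patients are "followed with a CT scan at day 0, day 2, day 4, day 6, and day 8".
- **Background.** "IVH often results in increased intracranial pressure (ICP) by direct mass effect", so raised ICP is also part of the disease.

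**The concern.** A safety comparison should count the harm that the protocol itself expects from the device. All four listed events (infection, bleeding, displacement, misplacement) can occur with any ventricular catheter. The two events tied to irrigation are absent, and the bracket carries no wording such as 'for example'.

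Followed literally, an excess of non-fatal raised ICP or hydrocephalus on IRRAflow would not move the comparison that guides stopping at 20 subjects. If the bracket was meant only as examples, the two sites could count different events towards the same total. The endpoint lists do not settle it: neither event is named there. The nearest entries are shunt dependency and an unspecified category of device-related complications, and neither is among the outcomes set for this look.

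**Working it through.** **1. Text against text.** Named irrigation risks: two. Those appearing in the four-item list: none. Mortality would catch fatal cases only.

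**2. Size.** The article gives no event rates and no test for this look, so there is no stated figure to reproduce. Assumptions: two-sided Fisher exact test, 10 v 10, each subject counted once, guide p < 0.20.

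| IRRAflow v control | p |
|---|---|
| 3 v 0 | 0.211 |
| 4 v 0 | 0.087 |
| 4 v 1 | 0.303 |
| 5 v 1 | 0.141 |
| 5 v 2 | 0.350 |
| 6 v 2 | 0.170 |
| 7 v 3 | 0.179 |

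A gap of about four subjects crosses the guide; these gaps of three do not.

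**3. Separate line or pooled total.** If the events were added to the total event count and compared by a conditional binomial test with probability 1/2, then 4 v 0 gives 2 × 0.5⁴ = 0.125. One other event per arm (5 v 1) gives 0.219, and two per arm (6 v 2) give 0.289. A few unrelated events hide the signal, so separate lines are better.

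**4. Chance that a separate line flags harm.** This is the sum over all (x, y) with x > y and Fisher p < 0.20 of Bin(x; 10, p_IRRAflow) × Bin(y; 10, p_control).

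| Assumed control rate | +20 points | +30 points | +40 points |
|---|---|---|---|
| 10% | 0.190 | 0.393 | 0.614 |
| 20% | 0.227 | 0.410 | 0.609 |
| 30% | 0.245 | 0.416 | 0.608 |

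With equal rates of 10%, 20%, 30% and 40% in both arms, the false harm flag per line is 0.5%, 2.4%, 4.2% and 5.4%.

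**5. Masking by occlusion.** The sample size assumes occlusion in 10% on IRRAflow and 35% on control, and a blocked drain can raise ICP. As an upper bound, let every occlusion raise ICP, independently of a 20% background rate.

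- Control: 1 − 0.80 × 0.65 = 48%.
- IRRAflow with a 20-point irrigation harm: 1 − 0.60 × 0.90 = 46%. The flag chance falls from 23% to about 5%.
- IRRAflow with a 40-point harm: 1 − 0.40 × 0.90 = 64%. The flag chance falls from 61% to about 19%.

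Under these background assumptions the truth lies between the two sets of figures.

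**6. The 10-patient look.** With 5 v 5, as reported under Trial status, Fisher needs 3 v 0 (p = 0.167); 4 v 1 gives 0.206. At a 20% control rate it flags a 30-point excess 18% of the time, against 41% at 10 v 10.

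**7. Timing.** Ten patients were enrolled from 13 January to 20 May 2022, which is 127 days. Another 127 days at that pace gives 24 September 2022 for the 20th, before publication on 29 December 2022.

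**The case against.** A reader might infer that the device's own harms go unmonitored, or that the 20-subject look is the only two-arm comparison with a p-value guide. The article supports neither. The 10-patient look has the same guide and counts severe events of any type. The DMC follows adverse events generally and weighs benefit against risk, and adverse events and shunt dependency are evaluated continuously. Nor do these harms count for nothing at the 20-subject look, since fatal cases enter through mortality. The alarms and the rule for reducing irrigation protect the individual patient.

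The bracket may also be illustrative. The governing phrase, events related to catheter treatment, could cover raised ICP from saline given through the catheter, and a journal article condenses the full protocol.

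Finally, a raised-ICP line is imperfect: the disease raises ICP in both arms, control-arm occlusions can offset an irrigation harm and give false reassurance, and detection is low in any case.

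Most of this stands and limits the weight of the point. It does not remove it. The article does state a list for this look, and the list is badly fixed against its own risk statement. A 10-patient look at severe events may miss an ICP rise managed by reducing irrigation, and bedside protection gives no comparison between arms. The occlusion argument changes how the line should be reported.

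**Conclusion.** The point holds as a minor one. Read as written, the 20-subject comparison leaves out non-fatal raised ICP and hydrocephalus, and other monitoring covers part of the gap. Closing it would flag a 20-point excess about 19% to 24% of the time and a 40-point excess about 61%, given a Fisher test and assumed control rates of 10% to 30%. For raised ICP the chance is lower to the extent that control-arm occlusions raise it. The 20-subject look has probably passed if enrolment kept its early pace, so the interim gain may not be realised. A reader might go on to infer that the efficacy result is compromised. It is not: the sample size, the primary analysis and the primary conclusion are unaffected.

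**What to change.** Keep mortality and the present catheter-event total, state whether the bracket is exhaustive, and add two lines to the monitored safety outcomes. Report each per arm, with each subject counted once per line:

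- **(a) Raised ICP after catheter placement:** 20 mmHg or above, sustained for a prespecified time, from readings charted on the same schedule in both arms, whether or not treatment was changed. Use charted readings and not device alarms, because only IRRAflow is described as having alarms. Show events with and without a concurrent catheter occlusion.
- **(b) New or worsening hydrocephalus:** judged against the day 0 CT, from the scans already scheduled.

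Use the same lines in the DMC's final data review if the 20-subject look has passed, with charted ICP for patients already enrolled.

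Cost: a short definition shared by the two sites (ICP duration, charting interval, what counts as worsening on CT) and two data fields, with no added visits, scans or patients. Downsides: disease-related events are counted in both arms, each line adds a false harm flag chance of 0.5% to 5.4% on the assumptions above, and detection stays low at 10 per arm, so an unremarkable line should not be read as reassurance.
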